Reported AEs will be followed until resolution whenever possible.

- 1. Study Termination

The study may be discontinued at the discretion of the Investigator (or designee), Sponsor, or Sponsor’s Medical Monitor if any of the following criteria are met:

- adverse events unknown to date
- increased frequency, severity, and/or duration of known, anticipated, or previously reported AEs (this may also apply to AEs defined at Check‑in as baseline signs and symptoms)
- At Day 90, <25 subjects observe reductions ≥50% from baseline for at least 2 of the following biomarkers of exposure: CEMA, S-PMA, 2-AN
- medical or ethical reasons affecting the continued performance of the study
- difficulties in the recruitment of subjects
- administrative reasons
- cancellation of product development.

A written statement fully documenting the reasons for study termination will be provided to the ethics committee (EC).

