1. ADVERSE EVENTS
   1. Definitions
      1. Adverse Events

The FDA modified risk tobacco product (MRTP) guidelines^26^ specify the following definition for AEs for tobacco products: an AE is any health-related event associated with the use of tobacco product in humans, which is adverse or unfavourable, whether or not it is considered related to the tobacco product, as defined by the MRTP guidelines.

An AE is defined as any untoward medical occurrence in a subject administered a study product, which does not necessarily have a causal relationship with the study product. An AE can therefore be any unfavourable and/or unintended sign (including an abnormal laboratory finding), symptom or disease temporally associated with the use of a study product, whether or not related to the study product.

- - 1. Serious Adverse Events

The FDA MRTP guidelines^26^ specify the following definitions for SAEs for tobacco products:

- results in death
- is life threatening
- requires inpatient hospitalisation or prolongation of existing hospitalisation
- results in persistent or significant disability/incapacity (disability is defined as a substantial disruption of a person’s ability to conduct normal life functions)
- is a congenital anomaly/birth defect

An important medical event that may not result in death, be life threatening or require hospitalisation may be considered a serious adverse experience when, based upon appropriate medical judgement, it may jeopardise the subject or may require medical or surgical intervention to prevent one of the outcomes listed in this definition. Examples of such medical events include allergic bronchospasm requiring intensive treatment in an emergency room or at home, blood dyscrasias or convulsions that do not result in inpatient hospitalisation, or the development of dependency or abuse.

Instances of death or congenital abnormality, if brought to the attention of the Investigator or their appropriately qualified designee at any time after last product use and considered by the Investigator or their appropriately qualified designee to be possibly related to the study product, will be reported to the Sponsor.

Definition of Life Threatening

An AE is life threatening if the subject was at immediate risk of death from the time of the event as it occurred; i.e. it does not refer to an event that might have caused death if it had occurred in a more serious form.

Definition of Hospitalisation

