Adverse events requiring hospitalisation should be considered serious. In general, hospitalisation signifies that the subject has been detained (usually involving an overnight stay) at the hospital or emergency ward for observation and/or treatment that would not have been appropriate at the clinical site. When in doubt as to whether hospitalisation occurred or was necessary, the AE should be considered serious.

Hospitalisation for elective surgery or routine clinical procedures, which are not the result of an AE, need not be considered AEs and should be recorded on a clinical assessment form and added to the eCRF. If anything untoward is reported during the procedure, this must be reported as an AE and either ‘serious’ or ‘non-serious’ attributed according to the usual criteria.

- 1. Assessment of Adverse Events

The condition of each subject will be monitored from the time of signing the ICF, to Check‑out at the Follow-up Visit. In addition, any signs or symptoms will be observed and elicited at each visit by open questioning, such as “How have you been feeling since your last visit ?”

Subjects will also be encouraged to spontaneously report AEs occurring at any other time during the study.

Any AEs and remedial action required will be recorded in the subject's source data. The nature, time of onset, duration and severity will be documented, together with the Investigator’s opinion of the relationship to product use.

Any clinically significant abnormalities identified during the course of the study will be followed-up until they return to normal or can be clinically explained.

- 1. Intensity of Adverse Events

The causal relationship between an AE and the study product is defined as follows:

**Not Related** The AE is definitely caused by the subject's clinical state or the study procedures/conditions.

**Unlikely Related** The temporal association between the AE and the product is such that the product is not likely to have any reasonable association with the AE.

**Possibly Related** The AE follows a reasonable temporal sequence from the time of product use but could have been produced by the subject's clinical state or the study procedures/conditions.

**Related** The AE follows a reasonable temporal sequence from the time of product use, abates upon discontinuation of the product and reappears when the product is reintroduced.

The severity of an AE will be recorded as one of the following:

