**Mild** Easily tolerated; does not interfere with normal daily activities; does not require intervention

**Moderate** Causes some interference with daily activities; minimal, local or non‑invasive intervention indicated

**Severe** Medically significant event; daily activities limited or completely halted; hospitalisation or prolongation of hospitalisation indicated

Every reasonable effort will be made to follow-up subjects who have an AE at Follow-up, if possible, until resolution.

Any AE assessed as related to the study product will be assessed for its expectedness. An AE will be regarded as ‘unexpected’ if its nature or severity is not consistent with information already known about the study product, and is not listed in the current Investigator’s Brochure (IB).^19^ The IB provides further detail on signs or symptoms that might be expected with the use of the study product, including information relating to malfunction or misuse.

- 1. SAE Reporting

All AEs occurring during this clinical study will be recorded from time of the subject signing the ICF until the end of the study. The Investigator or their appropriately qualified designee will review each event, grade its severity and assess its relationship to the product consumption and/or the study procedures. The date of onset, time of onset, and outcome of each event will be noted.

If any of the above AEs are serious, special procedures will be followed. The Investigator will report all SAEs to the Covance Pharmacovigilance and Drug Safety Services Department within 24 hours. This information must be sent by fax by filling out the serious AE form. Written reports must then be submitted within 48 hours, whether or not the serious events are deemed related to study procedures or products. The EC will be notified by these reports.

If an SAE occurs during this study, the Medical Monitor will be contacted.

- - 1. Abnormal Results of Laboratory Tests

Any clinical safety laboratory results that are outside of the normal reference range will be reviewed for clinical significance by the Investigator or their appropriately qualified designee. If the abnormal result is considered to be of clinical significance, it will be recorded as a concomitant disease (prior to enrolment) or an AE (after enrolment). As for other AEs, the relationship to the study product, intensity, seriousness and outcome of abnormal clinical safety laboratory results will be recorded.

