- - 1. Abnormal Results of Other Tests and Investigations

Any ongoing medical conditions or clinically relevant findings detected at Screening will be considered to be a concomitant disease and the subject’s eligibility to participate in the study will be reviewed. Any new, clinically relevant, abnormal findings or worsening of pre‑existing conditions detected during the study after the Screening Visit until the end of the study will be documented as an AE.

- 1. Reporting and Follow-up of Pregnancies

For pregnancies detected during the Screening Period and prior to first product use, the subject will be considered a screening failure and removed from the study. The diagnosed pregnancy will be captured on the screening failure eCRF.

All pregnancies occurring after signing the ICF and diagnosed after enrolment until the completion of the study must be reported to the Investigator. Any pregnancy potentially associated to exposure to the study product, including pregnancies spontaneously reported to the Investigator or their appropriately qualified designee after the end-of-study must be reported and followed-up. Potential association with exposure to the study product is defined as the conception date being calculated before the last exposure to the study product.

The Investigator will complete a Pregnancy Form for all pregnancies (including positive urine pregnancy tests). Pregnancies must be reported to the Medical Monitor, according to their standard procedures.

- 1. Adverse Events Leading to Withdrawal

Subjects who are withdrawn from the study because of an AE will undergo the following assessments and will return for a Follow-up Visit:

- Physical examination (symptom driven)
- Vital signs
- 12-lead ECG
- Review of AEs/SAEs
- Lung function tests
- Clinical laboratory evaluations
- Urine pregnancy test (female subjects only)

The Investigator will follow-up any AE until they have resolved, stabilized or an acceptable explanation has been found.

- 1. Investigational Product Misuse

Any occurrence of THP misuse by a subject will be documented by site staff. Misuse is defined as actions not in accordance with the product instructions.

Investigational product misuse may result in use-related hazards.

Use-related hazards are derived from the US FDA Medical Device Use Safety Guidance:^27^

- Hazards caused specifically by how a device is used.

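### Section 8.3 lets an adverse event be Related only after a positive rechallenge that the protocol does not plan, leaves a hole in the causality scale, and provides the expectedness assessment only for related events

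*Protocol*

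**What the plan says.** Section 8.3 of the protocol, headed Intensity of Adverse Events, gives a four-level causality scale: Not Related, Unlikely Related, Possibly Related and Related.

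- Related requires a reasonable temporal sequence from product use, and that the event "abates upon discontinuation of the product and reappears when the product is reintroduced". The conditions are joined by 'and', with no qualifier for cases where stopping or re-exposure did not occur.
- Possibly Related applies when an event "follows a reasonable temporal sequence from the time of product use but could have been produced by" some other source, either the clinical condition of the person or something in how the study is run. There is no level between this and Related.

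Later in the same section: "Any AE assessed as related to the study product will be assessed for its expectedness". An event counts as unexpected if its nature or severity does not fit what is known about the product and it is not listed in the Investigator's Brochure. No other causality category is sent to this assessment.

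Other sections bear on the point. Section 8.6 says "Subjects who are withdrawn from the study because of an AE will undergo the following assessments", lists safety examinations and a Follow-up Visit, and describes no reintroduction of the product. Section 8.4 requires SAE reports "whether or not the serious events are deemed related to study procedures or products". Section 6.5 lists "adverse events unknown to date" among the discretionary reasons for stopping the study.

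**The concern.** Monitoring the safety profile of THP users is a stated secondary objective (Section 2.2). Section 1.2.1 says that human health-effect data on these products are few and that their absolute risk still has to be quantified. In that setting the causality rating and the expected/unexpected label describe what the trial learned about product safety.

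A top category that depends on positive re-exposure suits transient, repeatable complaints. It excludes fatal, permanent and irreversible events whatever the strength of the other evidence. If expectedness is assessed only for that category, the excluded events also lose the classification that says whether they are new for the product. In a multi-centre study, sites that meet an event the scale does not cover may resolve it differently.

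**Working it through.** There is no figure to reproduce and no arithmetic applies. The check sets the definitions against the kinds of event that can occur.

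**Step 1: conditions for each level (Section 8.3).**

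- Related: plausible timing, abatement on stopping, and recurrence on reintroduction.
- Possibly Related: plausible timing, and another cause could have produced the event.
- Unlikely Related: timing such that the product has no reasonable association with the event.
- Not Related: definitely caused by the clinical state or by study procedures or conditions.

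**Step 2: events with plausible timing, placed on the scale.**

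| Event | Related? | Possibly Related? |
| --- | --- | --- |
| Transient; stops and recurs with product use | Yes | Also, if another cause is possible |
| Transient; product never stopped, or not resumed | No: abatement or recurrence not shown | Only if another cause is possible |
| Fatal or irreversible; another cause possible | No: cannot abate | Yes |
| Fatal or irreversible; no other cause apparent | No: cannot abate | No: condition not met |

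The last row, and the second row when no other cause is apparent, fit neither upper level. They do not fit the lower two either, because the timing is plausible and no other definite cause exists. The cases with the fewest competing explanations are thus the ones without a category.

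**Step 3: is re-exposure built into the plan?** No section describes a dechallenge or rechallenge procedure, and Section 8.6 describes none for subjects withdrawn because of an AE. Recurrence can be seen only by chance, when a subject pauses and resumes use.

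**Step 4: which events go to the expectedness assessment?** Section 8.3 names AEs assessed as related. The word is in lower case, so a looser sense that includes Possibly Related is conceivable. Against that, Section 8.1.2 spells out the lower threshold where it is meant: certain deaths and congenital abnormalities considered "to be possibly related to the study product, will be reported to the Sponsor". Section 8.3 also holds the protocol's only causality scale. The literal reading is the stronger one.

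**Step 5: what does not depend on the Related rating?** SAE reporting (Section 8.4), the termination criterion (Section 6.5), the recording of causality for every AE (Sections 8.2 and 8.4), and the summary of all safety data by study arm (Section 9.4).

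**The case against.** The case on the other side limits the reach of the point, and most of it stands.

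- *A reader might infer that virtually no product-caused AE could be rated Related, so that the trial would report almost none.* The documents do not support this. THP use is ad libitum (Section 3.1.3), and Section 12.2 says that subjects choose if and when they use it. The common product-related complaints in Section 1.2.1, such as dry mouth, dry throat and cough, could abate in a pause and recur on resumption. Events rated Possibly Related are still recorded and summarised.
- *A reader might infer that the termination criterion on unknown adverse events is disabled.* It is discretionary and mentions neither relatedness nor the expectedness assessment.
- *A reader might infer that serious hazards go unreported.* All SAEs go to pharmacovigilance within 24 hours whatever their causality, written reports follow within 48 hours, and the ethics committee is notified. The deep vein thrombosis in Section 1.2.1, rated possibly related in an earlier THP study on a scale the protocol does not give, was serious. A similar event here would take the full SAE route and could miss only the expectedness label.
- *The protocol attaches no timeline, rule or analysis to the unexpected label.* This is true, and it limits the practical loss.
- *Nothing says that only related AEs are assessed for expectedness.* This is also true, but the text provides for no others, and an ambiguity applied differently between sites needs the same repair.

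None of this answers the hole in the scale or the exclusion of irreversible events from Related.

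**Conclusion.** The point holds in a limited form. As written, an event that is irreversible, or that was never followed by re-exposure, cannot be Related. If it also has no alternative explanation, it fits none of the four levels and will be placed in a weaker one. Related counts are therefore understated to a degree that the protocol does not allow us to estimate, since it depends on how many events are irreversible and how often subjects happen to stop and resume use.

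On the plain reading, the same events also receive no expected or unexpected classification. This conclusion rests on taking the word related in the expectedness sentence as the defined category. The loss falls mainly on non-serious AEs and on the unexpectedness label of SAEs. It is a stated rule that misclassifies events under a stated safety objective, so it should be corrected. Serious-event reporting and the ability to stop the study are intact.

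**What to change.** Change two sentences in Section 8.3.

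1. Reword Related so that abatement on stopping and recurrence on re-use count as supporting evidence where they exist, not as requirements. For example: a plausible time course and no reasonable explanation in the subject's clinical state or the study procedures. Check the four definitions together so that every event has one category.
2. Begin the expectedness sentence with *Any AE assessed as possibly related or related*.

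Whether tables pool the two categories can stay with the SAP.

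The cost is small: the two sentences, the matching eCRF instructions, and more AEs to assess for expectedness. No visit, product or procedure changes. The synopsis shows that subjects had already been randomised before Amendment 7, so AEs already rated would need to be re-read under the new definitions if one scale is to cover the whole study.

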1. DATA ANALYSIS
   1. General Considerations

Covance will perform the data analysis. The results of the study will be reported in a clinical study report. A detailed Statistical Analysis Plan describing the methodology to be used will be issued to the Sponsor for review and finalised prior to database lock.

In general, continuous variables will be presented by means of descriptive statistics (n, mean, standard deviation, median, minimum and maximum) and categorical variables will be displayed by means of frequency tables and, where appropriate, shift tables. All summaries will be presented by study arm, sex, age, and timepoint.

All data collected for the study will be presented as data listings for each subject.

- 1. Analysis Populations

The statistical analysis will be based on separate, hierarchically organised analysis populations defined as the following:

**Safety population** - All subjects who smoked at least one cigarette or had at least 1 safety assessment on Day 1.

**Intent-to-treat population (ITT)** - All subjects who were assigned and had at least 1 valid assessment of a biomarker variable.

**Per-protocol population (PP)** - All subjects who had a valid assessment of a biomarker variable and completed study according to the protocol (no major protocol deviations).

All listings will be based on the safety population. The baseline and demographics data will be summarised on all 3 populations. The safety data will be summarised based on the safety population only and the remaining data will be summarised for both the ITT and PP populations.

If there is less than a 10% difference between the ITT and PP populations then the summaries will only be based on the PP population.

- 1. Statistical Analysis of Primary and Secondary Objectives

The primary objective will be examined by computing levels of biomarkers at each timepoint, i.e. baseline, 90, 180, and 360 days. These data will be compared between the THP arm (Arm B) and the main control arm (Arm A) using specific contrast tests from statistical models adjusted for baseline measurements. Data will be examined and may be transformed to ensure that any assumptions associated with statistical tests or models are obeyed. Alpha level across timepoints has been adjusted using the O’Brien-Fleming approach, with 0.0471 overall available alpha at Day 360, 0.0151 at Day 180, and 0.0006 at Day 90.^28^ The significance level has been allocated at each primary endpoint based on likelihood of success to detect a significant change in biomarker levels. At Day 360, statistical comparisons between THP and control will be performed at α= 0.0451 for AIx. The remainder alpha will be distributed equally (α= 0.001) for the other 2 primary endpoints. At Day 90, only changes in BoE are expected; therefore, only Total NNAL will be statistically assessed with α=0.0006**.** For the statistical analysis performed at Day 180, an overall α level of 0.0151 will be equally distributed between the 3 primary endpoints (0.00503). If any endpoint were to be significant at Day 90 or 180, it will not be statistically assessed at Day 180 and/or 360, as appropriate, and its assigned alpha level will be equally distributed between the remaining primary endpoints.

Similarly, biomarker measures in the secondary objectives will be examined by computing levels of biomarkers at each timepoint. These data will be compared between the THP and the main control arm using specific contrast tests from statistical models adjusted for baseline measurements. Statistical comparisons for secondary endpoints will be only performed if any of the primary endpoints is significant and using the alpha level released by primary endpoints. If the statistical comparison for Total NNAL is significant at Day 90, only the secondary BoE will be analysed at Day 90 using a 0.0006 significance level. Multiplicity adjustment for family wise error of secondary endpoints will be performed using Holm’s method. If any secondary endpoint were to be significant at Day 90 or 180, it will not be statistically assessed at Day 180 and/or 360, as appropriate.

Product use compliance is a critical part of this study, as failure to fully replace cigarettes with the THP product would reduce or cancel the expected biomarker changes that would be observed if the product is used as indicated. To aid compliance assessment we will use a haemoglobin adduct of acrylonitrile, CEVal. Acrylonitrile is below the detection limit in the THP product emissions but can be found in cigarette smoke. We will use different thresholds for CEVal in ancillary analyses to deduce product use compliance. These thresholds have been calculated based on a previous study where this biomarker was reported for a modified combustible prototype cigarette.

The interim analysis on Day 90 will be performed on a subset of subjects who were enrolled on to the study on or before the day that the 42^nd^ subject was enrolled on to Arm A, and were still enrolled on the study at Day 90. This was chosen to ensure that 30 subjects on Arm A were still enrolled on the study at Day 90 to give sufficient power to detect the statistical difference between the two arms for Total NNAL.

- 1. Safety Data Summary and Analysis

All safety data will be summarised for all safety parameters based on the safety population, stratified by study arm.

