Subjects in the continue-to-smoke/THP population will be randomised to Arm A or B. A randomisation scheme will be provided for the clinical sites. Each site will recruit a similar number of male and female subjects and a similar number of subjects ≤ 40 years old and > 40 years old at the time of randomisation.

Each site will receive 4 randomisation lists:

1. Males ≤ 40 years old.
2. Males > 40 years old.
3. Females ≤ 40 years old.
4. Females > 40 years old.

The allocation of subjects in each age/sex combination will be monitored on an ongoing basis during the study and if there is considered to be an imbalance between male and female subjects ≤ 40 years old and > 40 years old which could lead to problems when interpreting the data then the sites will be notified and will endeavour to prioritise the recruitment of subjects in the relevant category.

There will be no randomisation for subjects in the intend-to-quit population and never‑smoked populations; however, sites will endeavour to balance these populations in relation to male and female subjects and subjects ≤ 40 years old and > 40 years old.

- 1. Compliance

The study will be conducted in the ambulatory setting. Subjects will be required to comply with their randomised product or cessation aid, dependent on study arm, as indicated in Section 3.1.3.

Subjects will be instructed of the importance of complying with their randomised product (Arms A and B) or of not smoking cigarettes or using the THP (Arms D and E). Subjects will be asked to report any non-compliance via the automated eDiary (or paper diary if required) (Arms A, B and D) or using a paper diary (Arm E), and will be informed that compliance assessments will be conducted at selected clinic visits.

1. Selection of Study Population
   1. Selection of Study Population

Three populations will be recruited in total: 2 populations of smokers (Arms A, B, and D) and one population of subjects who have never smoked (Arm E).

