For Arms A and B, 265 male or female subjects who have smoked 10 to 30 cigarettes per day, inclusive, commercially available and/or roll your own, non-menthol CPD, and who are willing to switch to a THP will be enrolled in this study. For Arm D, 190 male or female subjects who smoke 10 to 30, inclusive, commercially available and/or roll your own, non‑menthol CPD and who are intending to cease all non-medicinal nicotine use will be enrolled in this study. For these 2 populations, subjects will have smoked for at least 5 years consecutively. The subjects’ smoking status will be verified using a urinary cotinine test (cotinine >200 ng/mL) and an exhaled CO measurement (exhaled CO ≥ 7 ppm; subjects may be rescreened if CO levels are < 7 ppm).^19^

For Arm E, 40 subjects who have never smoked (< 100 cigarettes in their life and none within 30 days prior to Screening) will be recruited.

Each site will recruit a similar number of male and female subjects and a similar number of subjects ≤ 40 years old and > 40 years old, as described in Section 4.4.

- 1. Determination of Sample Size

A target of 50 completed subjects in each of the Arms A, B, and D has been set for this study. This is based on power for the primary objective of multiple between-arm comparisons. Calculations are based on the primary biomarker requiring the largest sample size (Augmentation Index [AIx]) between test and control products. Specifically, the power calculation was based on the number of subjects required to perform a contrast based on the F-statistic with 90% power between the arm using THP1 and the smoking arm at Day 360. The sample size was determined to be adequate based on AIx with expected means of 25.7 and 17. 5 for smoker and THP arms, and a common standard deviation of 12.4.^20^

This calculation assumes an 80% change with respect to that observed in subjects quitting smoking and an alpha level of 0.0451, adjusted for timepoint multiplicity using O’Brien‑Fleming sequential approach.

Thirty completed subjects in Arm E has been determined empirically; no formal statistical analysis of sample size has been performed.

- 1. Inclusion Criteria

Subjects will be required to satisfy all of the following criteria at the Screening Visit, unless otherwise stated:

All Subjects:

1. Subjects will be:
   1. males or non-pregnant, non-lactating females

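### The stated A versus B model names the baseline measurement but none of the factors used to stratify randomisation (site, sex, age group): a small, conservative loss of efficiency

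*Protocol*

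**What the plan says.** Protocol section 4.4 (Randomisation) states: "Each site will receive 4 randomisation lists". The lists are defined by sex and by age at or below 40 versus above 40, the first being "Males ≤ 40 years old". The A/B allocation is therefore stratified by site, sex and age group. The same section has the age and sex mix monitored during recruitment, because an imbalance might hamper interpretation.

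Section 9.3 says that Arm B is compared with Arm A "using specific contrast tests from statistical models adjusted for baseline measurements". The phrase appears there twice, once for the primary and once for the secondary endpoints, and the synopsis repeats both. No stratification factor is named in any of the four places. Elsewhere in section 9, sex and age appear only as groupings for descriptive summaries.

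Section 9.1 leaves the detail to a further document: "A detailed Statistical Analysis Plan describing the methodology to be used will be issued". That plan was not available for this check.

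For the sample size, Determination of Sample Size sets "A target of 50 completed subjects in each of the Arms A, B, and D". It bases this on AIx "with 90% power between the arm using THP1 and the smoking arm at Day 360", with "expected means of 25.7 and 17. 5 for smoker and THP arms", "a common standard deviation of 12.4" and alpha 0.0451.

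**The concern.** Stratifying the randomisation balances the strata between arms, so differences between strata contribute little to the error of the treatment contrast. If the model leaves the strata out, their variance stays in the residual. The reported standard error is then larger than the design warrants, confidence intervals are too wide, and the test rejects less often than its nominal level.

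At stake is some efficiency on a comparison planned with 50 completers per arm and strict alphas. In section 9.3 these are 0.0451 for AIx and 0.001 for each of the other two primary endpoints at Day 360, 0.00503 each at Day 180, and 0.0006 for Total NNAL at Day 90. Secondary endpoints are tested only with alpha released by a significant primary endpoint, so a lost primary result would carry further down.

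The analysis would also not reflect factors that the sponsor thought important enough to stratify on and monitor. The text states an adjustment set and stops at baseline, so an SAP written to match it would omit them.

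**Working it through.** **Step 1: reproduce the plan's figure.** Inputs from Determination of Sample Size: difference 25.7 − 17.5 = 8.2, SD 12.4, alpha 0.0451 (two-sided assumed), power 90%.

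n per arm = 2 × (2.004 + 1.282)² × 12.4² / 8.2² = 2 × 10.80 × 2.287 ≈ 49.4, hence 50. This matches the protocol. A one-sided test would give 41 and does not match. At 50 per arm, power is 90.4% (normal approximation), 89.8% (noncentral t) and 90.0% (F contrast with three arms of 50). None of these uses a covariate, so the planned 90% does not depend on adjusting for baseline or strata.

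**Step 2: standard error.** Let R² be the share of the post-baseline variance explained by site, sex and age group. The documents do not give it; 2 to 10% is assumed. Adding the factors multiplies the standard error by √(1 − R²):

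- R² = 2%: 0.990, so leaving them out makes it 1/0.990, about 1% too wide
- R² = 5%: 0.975, about 2.6% too wide
- R² = 10%: 0.949, about 5.4% too wide

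This requires that balance within strata holds among the completers analysed.

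**Step 3: AIx power.** The comparator is the stated method, with baseline already in the model. Let ρ be the correlation between baseline and outcome (also not given; 0.5 to 0.7 assumed, with 0 as the extreme). Residual SD = 12.4 × √[(1 − ρ²)(1 − R²)]. Power is from the noncentral t, 50 per arm, alpha 0.0451.

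| ρ | SD, baseline only | Power, baseline only | + strata, R² 2% | R² 5% | R² 10% |
|---|---|---|---|---|---|
| 0.5 | 10.74 | 96.20% | 96.51% | 96.95% | 97.61% |
| 0.7 | 8.86 | 99.50% | 99.57% | 99.65% | 99.76% |
| 0 | 12.40 | 89.77% | 90.35% | 91.21% | 92.59% |

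The loss from leaving the factors out is:

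- ρ 0.5 to 0.7: 0.15 to 1.41 points for R² of 5 to 10%, and 0.07 to 0.31 points at R² of 2%
- ρ = 0: at most 92.59 − 89.77 = 2.8 points

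**Step 4: simulation.** 100 completers split about evenly within 16 assumed strata, strata entered as cells:

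| Assumed ρ, stratum share of total variance | Mean SE, baseline only → plus strata | Type I error, baseline only → plus strata (nominal 0.0451) | Power, baseline only → plus strata |
|---|---|---|---|
| 0.5, 20% | 2.15 → 2.06 | 0.036 → 0.045 | 97.1% → 97.6% |
| 0.7, 20% | 1.78 → 1.74 | 0.044 → 0.046 | 99.7% → 99.6% |
| 0.7, 40% | 1.77 → 1.67 | 0.043 → 0.047 | 99.5% → 99.5% |

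**Step 5: does balance survive?** Overall Study Design and Plan has 65 randomised to A and 200 to B, with at least 50 completing per arm. That allows up to 1 − 50/65 = 23% and 1 − 50/200 = 75% non-completion. Simulations of 65:200 allocation with random loss to 50:50 and assumed blocked lists put the size of the test without the strata at about 0.039 to 0.044 for R² = 10%. With unblocked lists it was nominal within simulation error. Adjusting for all 16 stratum cells gained little or nothing at R² of 10% or less.

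**The case against.** The strongest reply is that this belongs to the SAP. Section 9.3 does not restrict adjustment to baseline, names no model class, and sits under a section that defers the methodology. An SAP adding sex, age group and site would not contradict it. This largely stands. A reader might infer that the protocol excludes the stratification factors, and the documents do not support that. What remains is that the text specifies the adjustment set, repeats it, and stops short of the factors that shaped the allocation.

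The second reply is that nothing planned is missed. This stands in full: the 50 per arm reproduces without any covariate. A reader might also infer a sizeable loss by starting from 89.8% and crediting the strata with raising it to 92.6% or more. But 89.8% is the power with no baseline gain, not that of the stated model, and baseline AIx should already carry much of any sex, age or site effect.

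Third, the conservatism depends on balance among completers. The protocol describes lists but no blocks, does not give the number of sites, and allows heavy, unequal attrition. This also stands. Under exact balance the size formula 2 × [1 − Φ(2.004/√(1 − R²))] gives 0.035 at R² = 10%, and step 5 shows that to be an overstatement here.

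On the other side, the relative effect could be greater at the stricter alphas for Total NNAL and 8-Epi-PGF2α Type III. The protocol gives neither effect size nor SD for them, so this cannot be quantified.

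**Conclusion.** The point holds as a minor matter of efficiency and of consistency between design and analysis. Randomisation is stratified by site, sex and age group, and the stated A versus B model names only the baseline measurement among possible covariates.

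Followed literally, the analysis errs slightly on the conservative side, by the amounts in steps 2 and 3. Those rest on assumed values of R² and of the baseline correlation, and the standard-error figure also on balance among completers. The 90% target is met regardless and there is no inflation of type I error. The documents do not support calling this a validity error or a material loss of power, and the SAP may already include the factors.

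**What to change.** In section 9.3 and the synopsis, for both primary and secondary endpoints, state that the models adjust for the baseline measurement plus sex, age group (≤40 / >40) and site. Enter these as main effects rather than as a full set of stratum cells, because the cell version gained little or nothing in step 5. Treat site as random, or pool small sites, so that sparse sites do not destabilise the fit. Make the SAP match, or confirm that it already does.

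The cost is one sentence and a few degrees of freedom: one each for sex and age group, plus whatever site needs (the number of sites is not stated). All three factors are already recorded for the randomisation.
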